### Statistical methods

Primary analyses will follow the intention-to-treat principle. A per-protocol sensitivity analysis will include only participants who adhered to their assigned treatment until censoring. Baseline characteristics will be summarised using means with SDs, medians with IQRs or percentages. Differences at baseline will be tested using analysis of variance or χ^2^ tests.

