**Figure 1 F1:**
[figure not shown]
Visual representation of the study design. *Control physician. **Info from physician/pharmacy. CFS, Clinical Frailty Scale; EQ-5D-5L, EuroQol 5-Dimension 5-Level questionnaire; MACE, major adverse cardiovascular event; MoCA, Montreal Cognitive Assessment; ASAT, Aspartate Aminotransferase; ALAT, Alanine Aminotransferase; mRS, modified Rankin Scale; PROMIS-10, Patient-Reported Outcomes Measurement Information System 10-Question Short Form; TIA, transient ischaemic attack; (T-)MoCA, Telephone version of Montreal Cognitive Assessment; TOPICS-MDS, The Older Persons and Informal Caregivers Survey–Minimum DataSet.

Adherence to the intervention is monitored using pharmacy records. To minimise participant burden and enhance engagement, follow-up is conducted by phone or post, with no extra clinic visits or tests. The primary outcome (PROMIS-10) is relatively brief, which facilitates high completion rates. When questionnaires returned by post are incomplete, participants or their proxies are contacted by telephone to obtain the missing information. The study team will make repeated attempts when necessary to ensure that key outcomes are collected as completely as possible. At 12 and 24 months, general practitioners provide the most recent laboratory and blood pressure data available from routine care. Measurements performed within 6 months of the follow-up time point are accepted. Additionally, the SAFEST-RCT is part of the ‘Versneld Evalueren’ (Accelerated Evaluation) pilot by the national programme Care Evaluation and Appropriate Use (‘*Zorgevaluatie en Gepast Gebruik*’), which promotes rapid evaluation and implementation of healthcare innovations.

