### Sample size

We hypothesise that in frail older patients with recent ischaemic stroke or TIA, starting statins will cause a clinically relevant decrease in HRQoL without substantially improving MACE-free survival. For HRQoL, we expect baseline PROMIS-10 subscale scores of approximately 45, with an SD of 9.0 and a Minimal Clinically Important Difference of 4.5, approximated as 0.5 SD.^46 47^ Frailty and prior ischaemic stroke or TIA both reduce life expectancy in older adults.^11^,^13^ Based on previous studies, we estimate a 2-year survival rate of 52% in the control group.^48^,^50^ Cardiovascular events increase with age, and this older, frail cohort is therefore at higher baseline risk for MACE. Statin use in secondary prevention after ischaemic stroke or TIA in people of all ages has shown reductions in recurrent stroke (HR 0.89), myocardial infarction (HR 0.55) and cardiovascular death (HR 0.78).^51^ For our composite outcome of MACE-free survival in frail older patients, higher baseline risk and limited life expectancy support an HR estimate of 0.70. A total of 612 participants provide 99% power to detect a >4.5-point decrease in HRQoL and 80% power to detect an HR of 0.70 for MACE-free survival, using a two-sided alpha of 0.05, and accounting for 5% loss to follow-up.^52^ Loss to follow-up is expected to be minimal, as most discontinuations will involve study outcomes (MACE or non-cardiovascular death), and partial follow-up still contributes to the time-to-event analysis.

Sample size calculations are based on the Hotelling Lawley Trace test, using a linear exponent autoregressive model with a base correlation of 0.5 and a decay of 0.3.^53^ With approximately 6800 eligible patients annually in the Netherlands based on Dutch health insurance data,^54^ we expect to reach our recruitment target.

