#### Primary outcomes

HRQoL (PROMIS-10) will be analysed using a mixed model for repeated measures, with deceased patients scored as 0. Group differences over time will be reported with two-sided 95% CIs. MACE-free survival will be analysed using a time-to-event approach, with patients who withdraw early being censored at the time of withdrawal. The effect of statins will be expressed as an HR using a Cox regression model. Adjustments will be made for the type of event (TIA or ischaemic stroke), as these conditions may differ in baseline risk and prognosis. The assumption of proportionality will be tested, and Kaplan-Meier curves will visualise group differences in survival. Exploratory subgroup analyses of the primary outcomes will be performed by age, sex, type of event (ischaemic stroke or TIA), degree of frailty and LDL value.

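### The per-protocol analysis keeps only participants who adhered to the end of their own follow-up; if deviation is commoner in one arm this biases the HR, and it distorts the HRQoL contrast in an undetermined direction

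*Protocol article*

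**What the plan says.** Under Statistical methods the protocol article sets the main analysis set, "Primary analyses will follow the intention-to-treat principle", and then adds one sensitivity analysis: "A per-protocol sensitivity analysis will include only participants who adhered to their assigned treatment until censoring".

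Under Primary outcomes, "The effect of statins will be expressed as an HR using a Cox regression model". The only censoring rule given is for withdrawal: "MACE-free survival will be analysed using a time-to-event approach, with patients who withdraw early being censored at the time of withdrawal". Nothing is said about censoring at a departure from assigned treatment, or about weighting for it. PROMIS-10 is analysed with a mixed model in which participants who have died are given the value 0.

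The data for a different rule exist: "Adherence to the intervention is monitored using pharmacy records". The Discussion acknowledges that dispensing records show collection rather than intake.

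**The concern.** The sentence defines a subset by something that happens after randomisation, and judges it over a window whose length depends on the outcome. A participant whose follow-up ends early through an event has had little time to deviate and qualifies easily. One who stays event-free for 24 months has had the whole period in which to deviate, and is removed with all their event-free time if they do. The arm with more deviation is thereby enriched for events. This needs no link between stopping and prognosis; any such link would add bias in either direction.

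For HRQoL two selections act at once. Participants who stop because of side effects leave the set, which conceals the harm the Sample size section hypothesises. Early deaths, entered as 0, are over-retained in the arm with more deviation, which creates apparent harm.

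At stake is whether this analysis can corroborate or qualify the intention-to-treat result. As worded, it could disagree with it, or agree with it, purely through selection.

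**Working it through.** **Inputs from the Sample size section.** "we estimate a 2-year survival rate of 52% in the control group"; the design hazard ratio is 0.70, with 612 participants in total and 80% power for that outcome; two-sided alpha 0.05; 5% loss to follow-up. Follow-up is 24 months with 1:1 allocation.

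**Reproducing the plan's figure.** Schoenfeld events = 4(1.960 + 0.842)²/(ln 0.70)² = 247. Reading 52% as the control event-free proportion, the statin arm has 0.52^0.70 = 0.633, so the mean event probability is (0.480 + 0.367)/2 = 0.424. N = 247/0.424, about 584; 584/0.95 = 615, against 612 stated. The inputs are adequate for what follows.

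**Assumptions.** The documents give no stopping or starting rates. I take constant event rates, with control λ = −ln(0.52)/2 = 0.327 per year, and constant deviation rates κ independent of prognosis.

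**The rule in formulas.** A participant is kept if deviation comes after the earlier of event and 2 years. With m = λ + κ:
- kept with an event: E = (λ/m)(1 − e^(−2m))
- kept event-free: F = e^(−2m)
- person-years among the kept: P = λ[1 − e^(−2m)(1 + 2m)]/m² + 2F
- apparent event rate: E/P

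**Worked case, true HR 1.00, stopping 0.25 and starting 0.05 per year.**
- Control: m = 0.377, F = 0.471, E = 0.459, P = 1.343, rate 0.342.
- Statin: m = 0.577, F = 0.315, E = 0.388, P = 0.946, rate 0.410.
- Ratio 0.410/0.342 = 1.20. Excluded: 1 − 0.388 − 0.315 = 30% of the statin arm, and 1 − 0.459 − 0.471 = 7% of controls.

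For true HR 0.70 the statin λ is 0.229: F = 0.384, E = 0.295, P = 1.016, rate 0.290, ratio 0.290/0.342 = 0.85. Cox models on simulated data agree (1.20 and 0.85). Censoring at deviation returns 1.00 and 0.70.

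| Stopping vs starting, per year | True 1.00 appears as | True 0.70 appears as |
|---|---|---|
| 10% vs 5% | 1.05 | 0.74 |
| 25% vs 5% | 1.20 | 0.85 |
| 35% vs 5% | 1.32 | 0.93 |
| 15% vs 15% | 1.00 | 0.705 |

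**Sensitivity to the assumptions**, with deviation now expressed over two years:
- Stopping only in the statin arm at 10, 20, 30 or 40%: a true 1.00 becomes 1.05, 1.10, 1.17 or 1.26. With 290 per arm, a nominal 5% test under the null rejects in 7, 12, 25 or 46% of runs; censoring at stopping rejects in about 5%.
- Stopping 10%, control starting 30%: the bias reverses (0.89 from 1.00, and 0.63 from 0.70).
- Adherence judged over the full 24 months unless the event is fatal (half assumed fatal): 1.03 to 1.13 in place of 1.05 to 1.26, about half the bias.

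**HRQoL, the two opposing parts.**
- *Toward harm.* Take no true effect, survivors scoring 45, 52% now read as survival, and rates of 25% vs 5% per year. The share of zeros at 24 months among those kept is E/(E + F): 0.388/0.703 = 0.552 for statin, 0.459/0.930 = 0.494 for control. The false difference is −45 × (0.552 − 0.494) = −2.6 points. With assumed survival of 80% it is −1.7, and with 90% it is −1.0. The plan's minimal important difference is 4.5.
- *Toward no harm.* Assume 20% of the statin arm are intolerant and lose 9 points lastingly. The all-randomised difference is −0.20 × 9 = −1.8. If all of them stop, the adherent-only difference is 0; if half stop, it is −(0.10 × 9)/0.90 = −1.0. The shift is +0.8 to +1.8, and it applies to survivors only.

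These ranges overlap in size and have opposite signs.

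**The case against.** The best case for leaving the plan alone has four parts.

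- *The HR bias is conditional.* It needs unequal deviation between arms, and the article gives no rates; 1.20 rests on an assumed five-fold difference. This stands: the mechanism is certain, its size is not. Unequal rates are nonetheless plausible, because one arm must keep collecting a drug while the other is simply not prescribed one.
- *No primary conclusion depends on it.* Intention to treat is primary and keeps everyone who stops, and adverse events are recorded separately. This also stands. A reader might infer that the trial as a whole conceals statin intolerance; the documents do not support that, since the omission is confined to one supplementary subset.
- *The detail may lie in an unseen analysis plan.* How adherence is defined may well be there, as may further sensitivity analyses. But the article does fix the selection rule itself, and that is what is criticised.
- *The HRQoL direction.* A reader might infer that dropping people who stop for side effects must bias the per-protocol HRQoL result toward no harm. That overlooks the value of 0 given to deaths, which pulls the other way under the same selection.

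Labelling the analysis as descriptive only would also meet the concern, at the price of having no usable adherence-based estimate.

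**Conclusion.** The concern holds in a conditional form. The stated rule biases the per-protocol HR whenever deviation rates differ between arms, even if deviation is unrelated to prognosis. If statin stopping is the commoner deviation, the bias is against statins. At the assumed 25% vs 5% per year, it turns a null effect into 1.20 and shrinks the design effect of 0.70 to 0.85. It is about 5% of the HR at 10% vs 5% per year, close to nil at equal rates, and reversed if control starting dominates. The HRQoL contrast is distorted with undetermined sign. All sizes rest on assumed deviation rates, constant hazards, and the 52% figure read as event-free survival for the HR and as survival for HRQoL.

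The intention-to-treat results are unaffected. What is lost is the validity of the per-protocol analysis as a check on them. It should be changed, but it does not threaten the trial's main conclusions.

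**What to change.** Replace the subset rule. Keep all randomised participants and censor each at the first deviation from the assigned strategy: a dispensing gap longer than a pre-set length in the statin arm, or the first statin dispensing in controls. Weight the remaining follow-up by the inverse probability of staying uncensored, modelled from data already collected: baseline age, frailty score, laboratory values and MoCA, and time-updated falls, function and previous PROMIS-10. For HRQoL, apply the same weights to visits before deviation, and state how deaths before and after deviation enter.

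The cost is a change of wording and modest programming, with no new data collection. It can be settled well before data collection ends in January 2029. There are two limits to state alongside the result. The weights remove bias only through measured predictors of deviation, and the article mentions no recorded reason for stopping. Dispensing dates only approximate when intake stopped. Censoring without weights is adequate only if deviation is unrelated to prognosis.

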#### Primary outcomes

HRQoL (PROMIS-10) will be analysed using a mixed model for repeated measures, with deceased patients scored as 0. Group differences over time will be reported with two-sided 95% CIs. MACE-free survival will be analysed using a time-to-event approach, with patients who withdraw early being censored at the time of withdrawal. The effect of statins will be expressed as an HR using a Cox regression model. Adjustments will be made for the type of event (TIA or ischaemic stroke), as these conditions may differ in baseline risk and prognosis. The assumption of proportionality will be tested, and Kaplan-Meier curves will visualise group differences in survival. Exploratory subgroup analyses of the primary outcomes will be performed by age, sex, type of event (ischaemic stroke or TIA), degree of frailty and LDL value.

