### Participants

Eligible participants must meet the following criteria: (1) a neurologist-confirmed ischaemic stroke or TIA within 6 weeks prior to inclusion; (2) an age ≥70 at the time of the event; (3) not receiving statins at the time of the event; and (4) frailty, defined as a Clinical Frailty Scale (CFS) score of 4–7 pre-event and/or 6–7 post-event.^35^ The CFS evaluates domains such as daily and cognitive functioning and comorbidity, generating a frailty score from 1 (very fit) to 9 (terminally ill); scores ≥4 usually indicate frailty due to increased susceptibility to adverse outcomes, including reduced life expectancy.^35 36^

Exclusion criteria consist of: (1) a history of serious statin-related adverse reactions or contraindications (eg, severe liver disease); (2) very severe frailty (CFS ≥8); (3) inability to communicate in Dutch; (4) inability to respond to questions, independently or with the assistance of a proxy; (5) inability or unwillingness to provide written informed consent, independently or with the assistance of a proxy; (6) extremely high cardiovascular risk, defined as ≥1 cardiovascular event in the year before the index event; and (7) non-atherosclerotic stroke or TIA with no vascular risk factors.

Verbal consent to be contacted by an investigator is obtained by the treating neurologist. The local investigator then provides detailed study information (online supplemental appendix 2: participant information form) and obtains written informed consent, allowing at least 48 hours for consideration. Additional consent is sought for ancillary and follow-up studies. Randomisation is performed using Castor EDC (v.2025.1.2.0). Block (2:4) randomisation is used, stratified by hospital and type of event (ie, TIA or ischaemic stroke), with a 1:1 allocation ratio.

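### The 99% power for HRQoL is computed on a living-patient scale, but the analysis scores deaths as 0; on the analysed scale it holds only if mortality is low

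*Protocol article*

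**What the plan says.** Under Statistical methods, Primary outcomes, the rule is that "HRQoL (PROMIS-10) will be analysed using a mixed model for repeated measures, with deceased patients scored as 0". Group differences over time are to be reported with 95% confidence intervals; no single time point is named.

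Under Sample size, the inputs for the same outcome are "we expect baseline PROMIS-10 subscale scores of approximately 45, with an SD of 9.0 and a Minimal Clinically Important Difference of 4.5". The claim is "A total of 612 participants provide 99% power to detect a >4.5-point decrease in HRQoL". For the other primary outcome, the section claims "80% power to detect an HR of 0.70 for MACE-free survival". The error rate and the allowance for dropout behind these two claims are given as "using a two-sided alpha of 0.05, and accounting for 5% loss to follow-up". On method, the section states: "Sample size calculations are based on the Hotelling Lawley Trace test, using a linear exponent autoregressive model with a base correlation of 0.5". The decay parameter is 0.3. The same section says "we estimate a 2-year survival rate of 52% in the control group".

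**The concern.** A score of 0 lies five planning SDs below the planning mean of 45 (45/9.0 = 5). If close to half the patients die within two years, the analysed variable is a mixture of a spike at 0 and a distribution around 45. Its SD is far above 9, and a 4.5-point loss among survivors shrinks in proportion to the share still alive. The sample size section uses neither the larger SD nor the smaller difference.

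A loss of HRQoL on statins is the first part of the trial's stated hypothesis, and the results are meant for national guidelines. If the real power is well below 99%, a null HRQoL result would be taken as much firmer evidence against harm than it is. Because survival drives most of the variance, a survival difference could also be read as an HRQoL effect.

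**Working it through.** **Inputs from the article.** N = 612, allocated "with a 1:1 allocation ratio"; 5% loss, so 612 × 0.95 / 2 = 290.7 per arm; mean 45; SD 9.0; difference 4.5; two-sided alpha 0.05; control survival S = 0.52.

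**Reproducing the 99%.** With SD 9.0 and 290.7 per arm, SE = 9 × √(2/290.7) = 0.75 and power is above 99.9%. With only the expected survivors, 290.7 × 0.52 ≈ 151 per arm, SE = 9 × √(2/151) = 1.04 and power is about 99%. The stated figure is therefore met with living-patient inputs. This is a two-sample check, not the stated Hotelling-Lawley test.

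**Applying the death-as-0 rule at month 24.** With survivor mean m:

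- mean = S × m
- variance = S × 81 + S(1 − S) × m²

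Equal survival of 0.52 and a true 4.5-point loss in survivors give:

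- Control (m = 45): mean 23.40; variance 42.1 + 505.4 = 547.6; SD 23.4.
- Statin (m = 40.5): mean 21.06; variance 42.1 + 409.4 = 451.5; SD 21.2.
- Difference −2.34; SE = √((547.6 + 451.5)/290.7) = 1.85; z = 1.26; power = Φ(1.26 − 1.96) ≈ 24%.
- Share of control variance due to alive versus dead: 505.4/547.6 = 92%.
- Patients per arm for 99% power: (1.96 + 2.326)² × 999.1 / 2.34² ≈ 3,350, before loss.

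If 4.5 points is instead taken as the difference on the death-as-0 scale, with SD 23.4, power is 64%.

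**Averaging over visits.** The visit schedule is in a figure not shown, so it has to be assumed. Simulations of a baseline-adjusted average over visits gave 41% for two visits, 56 to 57% for four, and 65 to 72% for denser schedules. The independent re-run assumed exponential deaths, correlation 0.5, a constant effect and about 291 per arm.

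**What the 52% means.** It is worded as survival, but it reproduces the sample size as control-arm MACE-free survival. An HR of 0.70 needs 4 × (1.96 + 0.842)² / (ln 0.70)² ≈ 247 events. Event probabilities are 0.48 and 1 − 0.52^0.70 = 0.367, mean 0.424. That gives 247/0.424 ≈ 583, and 583/0.95 ≈ 614, against 612 stated. All-cause mortality may therefore be below 48%. With equal mortality and the same 4.5-point loss:

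| Dead by month 24 | Difference | SDs (control/statin) | Power, month 24 | Power, four assumed visits |
|---|---|---|---|---|
| 48% | −2.34 | 23.4 / 21.2 | 24% | 56–57% |
| 30% | −3.15 | 22.0 / 20.0 | 44% | 81–83% |
| 20% | −3.60 | 19.7 / 18.1 | 63% | 95% |
| 10% | −4.05 | 16.0 / 14.9 | 89% | over 99% |

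The alive/dead share of month-24 variance is 88%, 83% and 71% in the last three rows.

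**Unequal survival.** At 52% control survival, a 4.5-point loss is exactly cancelled at month 24 when statin-arm survival is 0.52 × 45/40.5 = 57.8%. That is an all-cause death HR of ln 0.578 / ln 0.52 ≈ 0.84.

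**The case against.** The strongest defence is that a composite that penalises death is a legitimate estimand. It keeps every randomised patient in the comparison and fits the intention-to-treat principle. That stands: scoring death as 0 is not in itself an error. But a composite has to be powered with the composite's own SD and difference.

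Month 24 is also the least favourable visit, and the article names no month-24 contrast. That stands too, which is why visit-averaged figures are given; at 48% mortality they remain well short of 99%. The doubt about the 52% also stands, and it is why the result is a range.

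A reader might infer that the rule turns the HRQoL primary into a mortality comparison whose sign will reverse. The article does not support that. Reversal at month 24 needs an all-cause death HR of about 0.84 or lower, and no such figure is given: 0.70 is for MACE-free survival, and 0.78 is for cardiovascular death in people of all ages. If statins acted only on cardiovascular death at 0.78, about (1 − 0.84)/0.22 = 73% of deaths would have to be cardiovascular. The stated hypothesis also expects no substantial gain in MACE-free survival; under it the consequence is lost power. Even assuming a death HR of 0.70, the month-24 difference is +2.2, and averaged over assumed visits only about −0.4 to +1.0.

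Nor does the outcome simply double count the other primary: non-cardiovascular deaths score 0 here but are not MACE. The linear exponent autoregressive model is a planning assumption, and the article does not say that it is the analysis covariance.

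**Conclusion.** The point holds as a mismatch between the variable powered and the variable analysed. If 52% is all-cause survival, survival is equal and survivors lose 4.5 points, power is about 24% at month 24 and about 41 to 72% averaged over assumed visits. If mortality is lower, power rises as tabulated, and 99% is supported only near 10% dead on a visit-averaged contrast.

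Mortality dominates the analysed variable across the range considered, so a survival difference could hide an HRQoL loss or pass for a gain. A change of sign is possible but conditional on a mortality effect that the article does not supply, and it is not part of the conclusion. The visit-averaged figures rest on assumed schedules.

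**What to change.** Make the Sample size and Primary outcomes sections describe the same variable, in one of two ways.

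1. **Keep the death-as-0 composite.** Restate its power as a range over plausible mortality, using the mixture SD and the diluted difference. State that the result is not a 4.5-point HRQoL change in patients. Report PROMIS-10 among those alive and all-cause mortality by arm beside it, with a rank-based composite (death below every live score) as a supportive analysis.
2. **Define the primary as HRQoL while alive.** SD 9.0 and about 99% power then apply. Report all-cause mortality by arm and the composite beside it.

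Which estimand to choose is a judgement on which statisticians differ. In either case, state whether the 52% is all-cause or MACE-free survival.

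The cost is wording in the protocol and analysis plan; no new data are needed. Data collection is due to run until January 2029, so the change can precede analysis. The downside of the first option is a less favourable stated power. The downside of the second is a contrast less protected by randomisation if survival differs between arms.

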## Methods

### Study design

This multicentre, prospective, randomised, open-label trial with blinded outcome evaluation is being performed across 22 Dutch hospitals (online supplemental appendix 1: participating study sites). The protocol follows the Standard Protocol Items: Recommendations for Interventional Trials 2013 guideline.^34^

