### Data collection and outcomes

The study evaluates the impact of statin prescription on two primary outcomes:

*HRQoL*, measured by the Patient-Reported Outcomes Measurement Information System 10-Question Short Form (PROMIS-10), which includes subscales for mental health and physical health.^39 40^*Three-point MACE-free survival*, defined as survival without any of the following MACEs: cardiovascular death, non-fatal myocardial infarction or non-fatal stroke. MACE events are self-reported by participants or reported by a proxy using a calendar returned every 3 months and are verified annually with treating physicians.

Secondary outcomes include functional outcome assessed using the modified Rankin Scale^41^; falling using a falls calendar; cognitive functioning using the Montreal Cognitive Assessment (MoCA)^42^ or the Telephone version of MoCA^43^; quality-adjusted life-years (QALYs) based on the EuroQol 5-Dimension 5-Level (EQ-5D-5L)^44^ questionnaire; and societal costs using The Older Persons and Informal Caregivers Survey–Minimum DataSet (TOPICS-MDS).^45^

At baseline, demographics, medication use and recent clinical metrics and laboratory values are extracted from the electronic patient record by local investigators. Furthermore, the PROMIS-10, MoCA, EQ-5D-5L, TOPICS-MDS and CFS are assessed. Follow-up continues for 24 months, with an optional 1-year extension for early enrollees. Assessment frequencies vary by outcome measure (figure 1). Participants, caregivers and local investigators are not blinded. However, all follow-up is conducted by investigators from the central research team who are blinded to treatment allocation.

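### Randomisation is stratified by hospital and event type, but the stated primary analyses adjust for event type only; the omission is conservative and small, and easily corrected

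*Protocol article*

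**What the plan says.** Under Participants, the protocol article describes the allocation: "Block (2:4) randomisation is used, stratified by hospital and type of event (ie, TIA or ischaemic stroke), with a 1:1 allocation ratio". Under Study design, the trial "is being performed across 22 Dutch hospitals".

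Under Primary outcomes, the two models are given as "HRQoL (PROMIS-10) will be analysed using a mixed model for repeated measures, with deceased patients scored as 0" and "The effect of statins will be expressed as an HR using a Cox regression model". The next sentence is the only one on adjustment in the primary analyses: "Adjustments will be made for the type of event (TIA or ischaemic stroke), as these conditions may differ in baseline risk and prognosis". It names event type and not hospital. It stands directly after the Cox model and does not say whether it also applies to the mixed model.

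Under Data collection and outcomes, the baseline assessment includes the quality-of-life instrument: "Furthermore, the PROMIS-10, MoCA, EQ-5D-5L, TOPICS-MDS and CFS are assessed". The Primary outcomes section does not say whether that baseline score enters the mixed model as a covariate, as one of the responses, or not at all.

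**The concern.** An analysis should reflect the restrictions placed on the randomisation. Stratified blocks balance the arms within each hospital, so the true sampling variance of the treatment difference contains almost no between-hospital component. A model that omits hospital still leaves that component in its residual variance. When hospitals differ in prognosis, the reported standard error is then too large, the confidence interval too wide and the test conservative.

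The article does more than stay silent here. It states an adjustment, gives prognosis as the reason, and lists one of the two stratification factors. A reader will take that as the adjustment set. At stake are calibration and a little precision, which matters more for MACE-free survival, planned at 80% power, than for PROMIS-10, planned at 99%.

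**Working it through.** **Inputs from the article.** N = 612, 22 hospitals, two event types, 1:1 allocation, 5% loss, two-sided alpha 0.05, HR 0.70, and 52% two-year survival in controls (read here as MACE-free survival). For PROMIS-10: "we expect baseline PROMIS-10 subscale scores of approximately 45", "with an SD of 9.0 and a Minimal Clinically Important Difference of 4.5, approximated as 0.5 SD", and a linear exponent autoregressive correlation with base 0.5 and decay 0.3.

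**The plan's own figures reproduce.**
- Events (Schoenfeld): 4 × (1.960 + 0.842)² / (ln 0.70)² = 247.
- Two-year event risks: 1 − 0.52 = 0.480 and 1 − 0.52^0.70 = 0.367, mean 0.424. Evaluable patients: 247 / 0.424 = 583. With 5% loss: 583 / 0.95 = 614, or 583 × 1.05 = 612. At 612 × 0.95 there are 246 expected events and power is 0.799.
- PROMIS-10, survivors only: 306 × 0.95 × 0.52 = 151 per arm. SE = 9 × √(2/151) = 1.035 and power is 0.992. The repeated-measures calculation itself was not rebuilt, because the visit schedule is in a figure not shown.

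**Thickness of the strata.** 22 × 2 = 44 strata. 612 / 44 = 13.9 patients and 246 / 44 = 5.6 events per stratum on average.

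**Hospital in a linear model.** Simulation with stratified blocks of 2 and 4, about 616 patients, SD 9, no treatment effect, 1,500 runs per row. Both models include event type; hospital was entered as indicators.

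| Assumed ICC | SE without hospital | SE with hospital | Change | Type I error without / with |
|---|---|---|---|---|
| 0 | 0.725 | 0.726 | +0.1% | 0.057 / 0.057 |
| 0.01 | 0.726 | 0.723 | −0.4% | 0.051 / 0.053 |
| 0.05 | 0.725 | 0.708 | −2.3% | 0.046 / 0.050 |
| 0.10 | 0.722 | 0.688 | −4.7% | 0.048 / 0.057 |

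The Monte Carlo SE of the type I error is about √(0.05 × 0.95 / 1500) = 0.006, so these runs show the SE change clearly but do not resolve the type I error.

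**Hospital in the Cox model.** Simulation with 581 patients, 52% of controls event-free at two years, log-normal hospital effects, 600 runs per setting. The comparison is hospital ignored versus a Cox model stratified by hospital.

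| Assumed SD of hospital log hazard | Power at HR 0.70, ignored / stratified | SE of log HR, ignored / stratified | Type I error, ignored / stratified |
|---|---|---|---|
| 0 | 0.802 / 0.793 | 0.129 / 0.130 | 0.045 / 0.047 |
| 0.2 | 0.810 / 0.805 | 0.129 / 0.129 | 0.040 / 0.040 |
| 0.4 | 0.793 / 0.805 | 0.128 / 0.129 | 0.028 / 0.038 |

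The Monte Carlo SE is √(0.8 × 0.2 / 600) = 0.016 for power and √(0.05 × 0.95 / 600) = 0.009 for type I error. Power differences are within noise. The last row points to a conservative test when hospital is ignored, but does not fix its size.

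**Baseline PROMIS-10 in the mixed model.** The planned correlation runs from 0.5 down to 0.5^1.3 = 0.406.
- Without deaths scored 0: r² = 0.25 to 0.165. The SE falls by 1 − √0.75 = 13.4% to 1 − √0.835 = 8.6%. Survivor power moves from 0.992 to 0.999 or 0.997.
- With deaths scored 0 at 24 months, 52% alive, and death independent of baseline: variance = 0.52 × (81 + 45²) − (0.52 × 45)² = 547.6, SD = 23.4. Correlation with baseline = 0.52 × r × 81 / (9 × 23.4) = 0.2r = 0.10 to 0.08. r² = 1.0% to 0.7%, and the SE falls by 0.5% or less.
- If a better baseline score predicts survival (assumed log-odds of 0.3, 0.5 or 0.8 per SD), the SE falls by about 2–3%, 5% or 9%.

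**The case against.** The best defence is that nothing here threatens validity. Any error is conservative, no hospital ICC is given, and the gain vanishes if hospitals are alike. Follow-up is central, by phone or post, which limits differences in measurement between sites. All of this stands, and it keeps the point modest. It does not explain why a stated adjustment follows one stratification factor and not the other.

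A reader might infer more, in four ways that the article does not support.
- *That baseline PROMIS-10 is left out.* The article is silent on its role. A mixed model for repeated measures can carry baseline as a covariate or as a response, and a condensed article commonly leaves this to the full protocol or SAP.
- *That using baseline would bring a large gain.* A 25% cut in variance at correlation 0.5 applies among survivors. The stated rule scores deaths as 0, which removes most of it at 24 months unless baseline strongly predicts survival. Power for PROMIS-10 is already 99%.
- *That precision is lost on both primary outcomes.* Stratifying the Cox model by hospital did not lower the SE of the log HR, and power stayed about the same. The article gives no link between baseline PROMIS-10 and MACE.
- *That age and the Clinical Frailty Scale must be added.* Randomisation does not require it. In a Cox model it changes the conditional HR being estimated, and the benefit depends on prognostic strength that the article does not give. It is a choice, not the repair of an error.

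**Conclusion.** The point holds in a limited form. Randomisation uses two stratification factors, the stated adjustment covers one, and its reach over the two primary models is unclear. The comparison is not biased. If hospitals differ, reported standard errors are somewhat too large: from essentially nothing at an ICC of 0 to 0.01 up to 4.7% at 0.10 in a linear model, with little change in Cox power. The sample size of 612 is unaffected.

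These sizes rest on assumed hospital effects, on equal average hospital size, and on reading 52% as MACE-free survival. The simulations used hospital indicators and a hospital-stratified Cox model; a random intercept and a shared frailty were not simulated. Including baseline PROMIS-10 is a sensible addition with a gain between under 1% and 13% of the SE, depending on the death rule and on how far baseline predicts survival.

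**What to change.** Before data lock, state in the analysis plan that both primary outcomes are analysed with both stratification factors:
- Mixed model: event type as a fixed effect and hospital as a random intercept.
- Cox model: event type as a fixed effect and hospital as a shared frailty. Full stratification on 44 cells with about 14 patients and 5 to 6 events each is too thin.
- Mixed model: baseline PROMIS-10 as a covariate by visit, or as a response in a constrained longitudinal model, with the choice stated.

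The cost is wording only. Hospital and event type are known from randomisation and baseline PROMIS-10 is already collected. The sample size and the data collection do not change.
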